**General Physical Examination Findings**

At screening, any clinically significant abnormality should be recorded as a preexisting condition. At the end of the study, any new clinically significant findings/abnormalities that meet the definition of an adverse event must also be recorded and documented as an adverse event.

**Hospitalization, Prolonged Hospitalization or Surgery**

Any adverse event that results in hospitalization or prolonged hospitalization should be documented and reported as an unanticipated adverse device effect unless specifically instructed otherwise in this protocol. Any condition responsible for surgery should be documented as an adverse event if the condition meets the criteria for an adverse event.

Neither the condition, hospitalization, prolonged hospitalization, nor surgery are reported as an adverse event in the following circumstances:

- Hospitalization or prolonged hospitalization for diagnostic or elective surgical procedures for a preexisting condition. Surgery should **not** be reported as an outcome

of an adverse event if the purpose of the surgery was elective or diagnostic and the outcome was uneventful

- Hospitalization or prolonged hospitalization required to allow efficacy measurement for the study
- Hospitalization or prolonged hospitalization for therapy of the target disease of the study, unless it is a worsening or increase in frequency of hospital admissions as judged by the clinical investigator.

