### 3.4 Primary Safety Endpoints

Data will be collected to determine:

- Incidence of emergency department and hospitalizations related to suicidality over a 12-month period.
- Incidence of adverse events, serious adverse events, and unanticipated adverse device effects.
- Any changes in cognition associated with treatment as assessed by the NIH Toolbox Cognition Battery.
- Any changes in auditory threshold assessments associated with treatment.

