| Adverse Events                                                             | Expected and
unrelated are
filed in the
triannual
DSMB
progress
reports | Expected and
unrelated are
filed with
annual
progress
reports | Expected and
unrelated are
filed with
annual
progress
reports | Not
applicable                                   |

| Protocol Violations | Annual progress reports                  | Annual progress reports                  | Annual progress reports                  | Not applicable |
|----------------------------|-------------------------------------------------|-------------------------------------------------|-------------------------------------------------|-----------------------|
| Pregnancy           | Within 5 business days upon notification | Within 5 business days upon notification | Within 5 business days upon notification | Not applicable |

Note – Some Adverse Events represent Unanticipated Problems that are required to be reported to OHRP (see: <https://www.hhs.gov/ohrp/regulations-and-policy/guidance/reviewing-unanticipated-problems/index.html>)

All adverse events occurring during the study, including those not meeting the criteria of an Unanticipated Adverse Device Effect (UADE) will be recorded on the appropriate case report form. Reporting time frames for the DSMB, FDA, and IRB are summarized in table 5. Expected clinical adverse events and anticipated adverse device effects include pain or discomfort under the treatment coil, eye pain, facial pain, facial numbness, toothache pain, skin pain, facial muscle twitching, blurred vision, seizures, cardiogenic syncope, and worsening mood symptoms. The DSMB will review all adverse events (expected and unexpected) in DSMB data reports submitted tri-annually. Unanticipated Adverse Device Effects (UADEs) will be reported to the DSMB, FDA, and IRB immediately (as noted in Table 5). Records of these events will be maintained and reports submitted to the FDA and IRB according to the regulatory requirements. Expected clinical adverse events and nonsignificant (not serious) clinical adverse events will be reported annually. Expected clinical adverse events and anticipated adverse device effects are those listed in Section 1.5.2.

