## 8.1 Definitions

### Unanticipated Adverse Device Effect (UADE)

A UADE is any serious adverse effect on health or safety or any life-threatening problem or death caused by, or associated with, a device if that effect, problem or death was not previously identified in nature, severity, or degree of incidence in the investigational plan or IDE application (including a supplementary plan or application), or any other unanticipated serious problem associated with a device that relates to the rights, safety, or welfare of subjects.

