**Adverse Effect (Event)**

Any untoward medical occurrence in a subject involved in clinical study of an investigational device; regardless of the causal relationship of the problem with the device or, if applicable, other study related treatment(s). Adverse events will be reported to the DSMB tri-annually.

**Associated with the investigational device:** There is a reasonable possibility that the adverse effect may have been caused by the investigational device. “Reasonable possibility” will be determined based on the PIs experience and relevant literature. These determinations will be reviewed with the study medical monitor, [name]) three times per year.

**Life-threatening adverse effect:** Any adverse effect that places the subject, in the view of either the investigator or the sponsor, at immediate risk of death from the effect **as it occurred**. It does not include a reaction that, had it occurred in a more severe form, might have caused death.

**Serious adverse effect:** An adverse effect is considered “serious” if, in the view of either the investigator or the sponsor, it results in any of the following outcomes:

- death
- a life-threatening AE
- inpatient hospitalization or prolongation of existing hospitalization
- a persistent or significant disability/incapacity
- a congenital anomaly/birth defect.

**Unanticipated adverse effect:** Any adverse effect, the nature, specificity, severity, or frequency of which is not consistent with the risk information in the clinical study protocol or elsewhere in the current IDE application.

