### **8.3 Sponsor-Investigator Reporting of Unanticipated Adverse Device Effects and Unanticipated Problems**

When an adverse event has been identified, the study team will take appropriate action necessary to protect the study participant and then complete the Study Adverse Event Worksheet and log. The sponsor-investigator will evaluate the event and determine the necessary follow-up and reporting required.

The sponsor-investigator will promptly review documented Unanticipated Adverse Device Effects and as necessary shall report the results of such evaluation to the FDA and DSMB within 10 working days and to the Mayo IRB within 5 working days of initial notice of the effect. Thereafter the sponsor-investigator will submit such additional reports concerning the effect as requested.

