##### ***Study Stopping Rules***

In order to ensure that subjects are not exposed to risks across the study and that risks are evaluated the follow are study stopping rules. **These stopping rules apply to the two-week period when subjects are receiving the study intervention (active or sham sequential**

**bilateral aTBS). These rules do not apply to subjects in the naturalistic 1-year follow-up portion of the study.** There are no pre-determined stopping rules for events that take place during the follow up-period as suicide attempts and psychiatric hospitalizations are expected to be common events. Adverse events that occur while subjects are in the follow up period will be tracked during the long term naturalistic follow up. The study team will be evaluating the expectedness and relatedness of these events; the IRB, DSMB, FDA will provide oversight of these determinations. AEs and SAEs will be reported and reviewed by the DSMB in the data reports according to the timeframes delineated in Section 8, Table 5.

- i. Two subjects who experience seizure(s).
- ii. One or more subject(s) who experiences status epilepticus.
- iii. One or more subject(s) who attempts or dies by suicide.
- iv. Two or more Serious Adverse Events--related to the study intervention and occurring within the 2-week treatment period--in one or more subjects.

In the event these study stopping rules are met, enrollment of new subjects will cease, but all study activities will continue for enrolled subjects. The PI will consult with the DSMB and the FDA within 10 business days upon initial notice of meeting stopping rules.

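### Section 8.1 makes hospitalisation the default trigger for the UADE label, which contradicts the protocol's own UADE definition and Table 5 and can only add to a listed primary safety endpoint

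*Protocol*

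**What the plan says.** Section 8.1, under the heading on hospitalisation and surgery, sets a default: an adverse event that results in a new or prolonged admission "should be documented and reported as an unanticipated adverse device effect unless specifically instructed otherwise in this protocol". Three circumstances follow in which nothing is reported as an adverse event: elective or diagnostic procedures for a preexisting condition, stays needed for efficacy measurement, and admission to treat the target disease. The third no longer applies if, in the investigator's view, the admission is a worsening or admissions have become more frequent.

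The UADE definition in Section 8.1 covers a serious effect "caused by, or associated with, a device if that effect, problem or death was not previously identified in nature, severity, or degree of incidence". What counts as identified is set by the protocol and the IDE submission. A second limb covers other serious problems that are both unforeseen and tied to the device. An adverse event is defined in the same section "regardless of the causal relationship of the problem with the device".

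Section 3.4 lists as a primary safety endpoint: "Incidence of adverse events, serious adverse events, and unanticipated adverse device effects". The Study Stopping Rules in Section 8.5 say of the follow-up period that "suicide attempts and psychiatric hospitalizations are expected to be common events".

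On timing, Table 5 gives 5 business days for UADE reports to DSMB, FDA and IRB, and the text after it says such effects are reported at once, pointing to Table 5. Section 8.3 says that the sponsor-investigator "shall report the results of such evaluation to the FDA and DSMB within 10 working days".

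**The concern.** Admission to hospital makes an event serious. It does not make it device-related or unforeseen. The default in Section 8.1 applies the UADE label on the first property alone.

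This matters here because the trial enrols adolescents with suicidal ideation and records adverse events for 12 months after treatment, in both arms. An admission unrelated to stimulation, or of a kind the protocol already lists as a risk, would enter the category meant for unforeseen device harm. At stake are the meaning of one component of the primary safety endpoints, and the class and reporting route of each such admission.

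**Working it through.** The documents give no UADE count or admission rate, so there is no figure to reproduce. The check sets the texts side by side.

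**1. Conditions for the label.**

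| Condition | UADE definition (8.1) | Hospitalisation default (8.1) |
|---|---|---|
| Serious | required | met by the admission itself |
| Device-associated | required | not tested |
| Not previously identified | required | not tested |

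Adverse events are defined without regard to cause, so the events that feed the default include unrelated ones.

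**2. The exceptions.** Each says that an admission is not an adverse event at all. None asks whether the device was involved or whether the event was foreseen. The target-disease exception lapses on worsening. Yet Section 8 lists worsening mood symptoms as expected, and Section 1.5.2, whose risks Section 8 treats as anticipated, covers clinical deterioration and worsening suicidal ideation, with inpatient referral as indicated.

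**3. Table 5.** An admission that counts as an adverse event is a serious adverse event under Section 8.1.
- If unrelated, Table 5 sends it to the triannual DSMB reports and the annual FDA and IRB reports. As a UADE, it goes to all three within 5 business days.
- If expected and related, Table 5 already sets 5 business days. The clock is the same, but the class differs, and under Section 8.3.2 a UADE also calls for Form 3500A to FDA.

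**4. Case-by-case review.** Section 8.2 has the sponsor-investigator determine causality and seriousness for each documented effect. Section 8.5 has the study team evaluate expectedness and relatedness of follow-up events. The default assigns the label before either step.

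**5. Direction and unit of effect.** An event that meets the UADE definition is a UADE with or without the default. The default therefore removes no events and can only add some. On the target of 80 subjects randomised 1:1 (40 per arm), each subject who is a UADE case only because of the default adds
- 1/80 = 1.25 percentage points to overall UADE incidence, and
- 1/40 = 2.5 percentage points in that subject's arm.

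The number of such subjects is not in the documents.

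**6. Timing.** For UADE reports to FDA and DSMB, Table 5 says 5 business days and Section 8.3 says 10 working days. Section 8.3.2 gives an outer limit of 10 working days for the FDA form. The IRB limit is 5 days in both Table 5 and Section 8.3.

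**The case against.** The strongest reply is that the default carries its own limit: it yields to any specific instruction elsewhere in the protocol. Section 8.5 names psychiatric hospitalisations in follow-up, requires review of their expectedness and relatedness under IRB, DSMB and FDA oversight, and points to Table 5. Section 8.2 keeps a causality assessment, the medical monitor reviews device association three times a year, and Form 3500A is due only for an effect determined to be a UADE. A sensible team may therefore never apply the default literally.

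This softens the point but does not remove it. None of those passages refers to the hospitalisation rule. If Table 5 is the exception, its rows already cover serious events that are unexpected and related, expected and related, or unrelated, which leaves the default almost nothing to govern. The sentence is then either in conflict or redundant.

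A second reply is that Section 3.4 lists suicidality admissions separately and that nothing says UADEs will be tabulated by the default. That is fair: the effect on the endpoint depends on the default being followed.

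On timing, notifying an event and reporting the results of its evaluation can be different acts, and a report within 5 business days would normally also fall within 10 working days. The mismatch is real but minor.

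**Conclusion.** The point holds as an inconsistency in safety-reporting definitions. The default contradicts the UADE definition and the Table 5 rows for unrelated and for expected related serious events, and it fits poorly with the case-by-case review in Sections 8.2 and 8.5. Followed literally, it pushes UADE incidence upward in both arms, including through admissions for worsening of the target disease. The size cannot be determined from the documents.

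A reader might infer more. The documents do not support any of the following:
- *Every admission becomes a UADE.* The exceptions and the clause yielding to other instructions limit the rule.
- *The UADE count would consist mostly of expected psychiatric admissions, or some specific number of them.* No admission rate is given, and the share that would count as worsening is left to the investigator.
- *A real device signal would be hidden.* There is a randomised sham arm, suicidality admissions and serious adverse events have their own entries in Section 3.4, and causality is assessed for each event.

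The matter does not touch the primary efficacy analysis, the sample size or the randomisation.

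**What to change.** In the hospitalisation paragraph of Section 8.1, replace *unanticipated adverse device effect* with *serious adverse event*. Add that the event is classified as a UADE only if it meets the UADE definition in that section. This restates the protocol's own definition and lets Table 5 route each admission by relatedness and expectedness.

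In the same amendment, reconcile the UADE time limits in Table 5, the Section 8 text, Section 8.3 and Section 8.3.2. If initial notice and the evaluation report are meant to have different limits, say which limit belongs to which.

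The cost is a wording amendment. No procedure, data collection or clinical management changes.

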### **Post-study Adverse Event**

All unresolved adverse events should be followed by the investigator until the events are resolved, the subject is lost to follow-up, or the adverse event is otherwise explained. The study team will report unresolved adverse events to the DSMB when the subject exits the study. The study team will track adverse events through resolution and report to the DSMB as feasible (if the patient can be contacted or monitored). The study team will report unresolved adverse events that cannot be tracked through resolution to the DSMB (the subject cannot be contacted or is unwilling to have contact with the study team). At the last scheduled visit, the study team will instruct each subject to report, to the local investigator, any subsequent event(s) that the subject, or the subject's personal physician, believes might reasonably be related to participation in this study. The local investigator should notify the study regulatory sponsor of any death or adverse event occurring at any time after a subject has discontinued or terminated study participation that may reasonably be related to this study. The sponsor should also be notified if the local investigator should become aware of the development of problems, cancer or of a congenital anomaly in a subsequently conceived offspring of a subject that has participated in this study.

### **Preexisting Condition**

A preexisting condition is one that is present at the start of the study. A preexisting condition should be recorded as an adverse event if the frequency, intensity, or the character of the condition worsens during the study period.

### **Unanticipated Problems Involving Risk to Subjects or Others (UPIRTSO)**

Any unanticipated problem or adverse event that meets all of the following three criteria:

- **Serious**: Serious problems or events that results in significant harm, (which may be physical, psychological, financial, social, economic, or legal) or increased risk for the subject or others (including individuals who are not research subjects). These include: (1) death; (2) life threatening adverse experience; (3) hospitalization - inpatient, new, or prolonged; (4) disability/incapacity - persistent or significant; (5) birth defect/anomaly; (6) breach of confidentiality and (7) other problems, events, or new information (i.e. publications, DSMB reports, interim findings, product labeling change) that in the opinion of the local investigator may adversely affect the rights, safety, or welfare of the subjects or others, or substantially compromise the research data, **AND**
- **Unanticipated**: (i.e. unexpected) problems or events are those that are not already described as potential risks in the protocol, consent document, not listed in the Investigator's Brochure, or not part of an underlying disease. A problem or event is

"unanticipated" when it was unforeseeable at the time of its occurrence. A problem or event is "unanticipated" when it occurs at an increased frequency or at an increased severity than expected, **AND**

- Related: A problem or event is "related" if it is possibly related to the research procedures.

### **Adverse Event Reporting Period**

For this study, the study treatment follow-up period is defined as 12 months following the last administration of study treatment.

### **8.2 Recording of Adverse Events**

At each contact with the subject, the investigator must seek information on adverse events by specific questioning and, as appropriate, by examination. Study subjects will be routinely questioned about adverse effects at study visits. Information on all adverse events should be recorded immediately in the source document, and also in the appropriate adverse event section of the case report form (CRF) or in a separate adverse event worksheet. All clearly related signs, symptoms, and abnormal diagnostic, laboratory or procedure results should be recorded in the source document.

All adverse events occurring during the study period must be recorded. All observed or volunteered adverse effects (serious or non-serious) and abnormal test findings, regardless of the treatment group if applicable or suspected causal relationship to the investigational device or if applicable other study treatment or diagnostic product(s) will be recorded in the subjects' case history. For all adverse effects sufficient information will be pursued and/or obtained as to permit; an adequate determination of the outcome, an assessment of the causal relationship between the adverse effect and the investigational device or, if applicable other study treatment or diagnostic product. The clinical course of each event should be followed until resolution, stabilization, or until it has been ultimately determined that the study treatment or participation is not the probable cause. Serious adverse events that are still ongoing at the end of the study period must be followed up, to determine the final outcome. Any serious adverse event that occurs after the study period and is considered to be at least possibly related to the study treatment or study participation should be recorded and reported immediately.

A form should be created for capturing information related to adverse events and submitted with the IDE application to the FDA.

Recommended information to capture on the Adverse Event CRF:

- Subject Study Number/Identifier
- Device information (model and serial number)
- Date of event onset
- Description of the event
- Indication if study treatment was discontinued, or if investigational device was removed
- Subject current status, or if the event was resolved

- Principal Investigator assessment of if the event was serious and justification for determination
- Principal Investigator assessment of causality and relationship to study treatment.

#### Causality and severity assessment

The sponsor-investigator will promptly review documented adverse effects and abnormal test findings to determine 1) if the abnormal test finding should be classified as an adverse effect; 2) if there is a reasonable possibility that the adverse effect was caused by the investigational device or other study treatments; and 3) if the adverse effect meets the criteria for a serious adverse effect.

If the sponsor-investigator's final determination of causality is "unknown and of questionable relationship to the investigational device or other study treatments," the adverse effect will be classified as associated with the use of the investigational device or other study treatments for reporting purposes. If the sponsor-investigator's final determination of causality is "unknown but not related to the investigational device or other study treatments," this determination and the rationale for the determination will be documented in the respective subject's case history.

